##### Physical function

The timed up-and-go test, four-square step test and 30-second sit-to-stand test will be used to assess muscle function.

The timed up-and-go test is a measure of dynamic balance during three commonly performed functional activities: standing up from and sitting down in a chair, walking, and turning [41]. Briefly, participants will be seated in a chair (height 45 cm) that will be placed at the end of a marked 3 m walkway. On the command ‘go’, participants will be instructed to stand up, walk at a comfortable speed for 3 m, turn, walk back to the chair and sit down. To minimize any ceiling effects and make the test more challenging, the participants will also be instructed to start counting backwards in threes from a random number. All participants will be given a practice trial and one test run. A stopwatch will be used to record the time taken (in seconds) to complete the test. This test has an established interrater reliability, with an intraclass correlation of 0.99 [42].

The four-square step test is a clinical test used to assess dynamic standing balance and stepping speed in four different directions [43]. This test has been shown to have high interrater (intraclass correlation, 0.99) and retest reliability (intraclass correlation, 0.98) [43]. To complete this test, participants will be required to step forwards, sideways and backwards over four canes resting flat on the floor in a cross formation, moving first in a clockwise and then in a counterclockwise direction to return to the starting position. Participants will be instructed to complete the task as quickly as possible without touching or stepping on the canes, and if possible, to face forwards during the entire sequence. They will also be instructed to ensure that both feet make contact with the floor in each square. After one practice trial, participants will complete the test and the time (in seconds) taken to complete the sequence will be measured with a stopwatch and recorded as the final score.

The 30-second sit-to-stand test provides a measure of lower-extremity muscle strength and function and is administered in a chair without arms [44]. Participants start from a seated position in the chair, with arms folded across the chest, and are instructed to stand fully upright and then return to the seated position at their own pace as many times as possible in 30 seconds. The final score will be the number of complete stands recorded during this time. This test has been shown to have good reliability with a test-retest intraclass correlation of 0.84 to 0.92 in a community-dwelling sample of older men and women aged 60 years and over [44].

##### Dietary habits

The Anti-Cancer Council Food Frequency questionnaire will be used to quantify habitual eating habits and provide data on macro- and micronutrient intake [45]. Dietary data collected from the Anti-Cancer Council Food Frequency questionnaire will be supplemented with 24-hour dietary recollections completed at baseline, 12 and 24 weeks. Participants will be contacted (via phone) by the research staff (trained in completing food recall tasks) and asked to report all food and drink consumed over the previous 24-hour period. A standard script will be used and the ‘triple pass’ method will be utilized to maximize the ability of respondents to recall what was consumed. Household measures (measuring cups, plates, bowls and glasses) will be used to help estimate food portion sizes and participants will be provided with a standard portion size booklet. The data collected from the 24-hour recalls will be entered and analyzed using Australia-specific dietary analysis software (FoodWorks, Xyris software, Highgate Hill, Queensland, Australia).

##### Anthropometry

Height will be measured to the nearest 0.1 cm with a wall-mounted stadiometer and body weight to the nearest 0.1 kg using calibrated electronic digital scales. Waist circumference will be measured on a horizontal plane, 2 cm proximal to the uppermost lateral border of the right iliac crest.

##### Physical activity

Total leisure and recreational physical activity time (hours per week) will be assessed using the Community Healthy Activities Model Program for Seniors physical activity questionnaire. This questionnaire has been specifically designed for use in older adults and found to be reliable, valid and sensitive to change [46]. Participants will document the frequency and duration of their participation in a ‘typical week’ of the preceding four weeks. The results will be reported as estimated kilojoules per week spent in moderate to high-intensity activities.

##### Health and medical history and medication use

All participants will complete a lifestyle questionnaire to obtain information on education background, current and previous employment details, history of diseases or illnesses, family history of diabetes, smoking history, current medication and dietary supplement use, average weekly alcohol consumption, weekly television viewing and sitting time, and sun exposure habits. For women, menstrual history, including age of onset of menopause and menstrual cycle regularity, together with use of oral contraceptive and hormone replacement therapy will be evaluated. Information on any alterations to or new medication prescribed by the participants’ doctors will also be collected by research staff via the monthly phone calls. Information recorded will include medication name, dose prescribed and daily quantity taken.

##### Health-related quality of life

Health-related quality of life will be assessed using the Short Form (36) version 2 questionnaire, which is a general measure of health status including eight scales: physical functioning, physical role functioning, bodily pain, general health perceptions, vitality, social role functioning, emotional role functioning and mental health [47]. This test yields a score from 0 to 100, where 0 represents the lowest and 100 represents the highest quality of life. Reliability scores of above 0.80 and empirical validities of 0.80 to 0.90 have been reported in the literature for both the physical and mental health measures [47].

##### Cognitive function

Cognitive function will be assessed using the CogState Brief Battery computerized tests [48], which provide sensitive and valid measurement of a range of different cognitive functions [49, 50]. The battery of tests that will be used for this study include: measures of executive function and spatial problem solving (Groton maze learning test), psychomotor function and speed of processing (detection task), visual attention (identification task), visual learning with a pattern separation model (one-card learning task) and working memory and attention (one-back task). Specific details about these five tests have been described previously [49–52]; all tests have been designed for repeated administration with minimal practice or learning effects.

##### Compliance

Compliance in taking the prescribed protein and vitamin D will be evaluated via self-completed compliance calendars and cross-referenced by counting remaining sachets and vitamin D capsules returned at each subsequent follow-up appointment. Compliance with the exercise programme will be evaluated via self-completed exercise cards, which will be initialled by the participant and viewed (signed off) by the trainer after each session and collected by the research staff from each health and fitness centre at approximately two-monthly intervals throughout the intervention.

##### Adverse events

Any adverse events associated with the exercise programme or supplements will be recorded by the research staff during the monthly phone calls to participants. For this study, an adverse event is defined as any health-related unfavourable or unintended medical occurrence (sign, symptom, syndrome, illness) that develops or worsens during the period of observation in the trial. All adverse events will be assessed for seriousness, causality and expectedness by the research staff and recorded and monitored during the trial.

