## Methods/Design

### Study design

This study is a 6-month, two-arm, parallel, randomized controlled trial. Participants with confirmed type 2 diabetes will be asked to participate in a structured PRT programme, based on the community-based *Lift for Life®* programme, and randomly allocated to receive either a whey-protein powdered drink plus vitamin D supplements, or no additional powder or supplements. A matched placebo powder was deemed inappropriate for this trial, as the use of food additives, such as maltodextrin, has the potential to influence the outcome measures (for example, glycaemic control). The selection of a two-arm design (for example, the lack of a true ‘non-exercise’ control arm) is consistent with our primary research aim, which seeks to examine whether whey-protein plus vitamin D can enhance the health benefits of PRT in older adults with type 2 diabetes. The trial is managed by the Centre for Physical Activity and Nutrition Research at Deakin University, Burwood, Melbourne, Victoria, Australia and is funded by a National Health and Medical Research Council Project Grant (ID1046269). The study has been approved by the Deakin University Human Research Ethics Committee (HREC 2013–050), and is registered with the Australian and New Zealand Clinical Trials Registry (ACTRN12613000592741).

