The 24-week *Lift for Life®* PRT programme is divided into three phases (bronze, silver, gold), each 8 weeks in duration. During the initial phase (bronze), participants receive education on the benefits of the programme, safety and correct exercise techniques and are asked to attend two supervised exercise sessions per week. After 8 weeks, all programmes will be reviewed and a new customized programme will be designed for each participant (silver), but with the aim of participating in one additional unsupervised exercise session to achieve the goal of three PRT sessions per week. The final 8-week phase (gold) is a replication of the previous phase with a new customized and progressively challenging programme. Throughout the programme, all completed exercises, sets and repetitions for each session will be recorded on *Lift for Life®* exercise cards, to monitor progression and compliance. Further details of the programme, including examples of the exercises and intensity prescribed, have been reported previously [14].

One of the challenges when implementing exercise programmes in community settings is that of enhancing adoption and adherence to these programmes. At the foundation of *Lift for Life®* and central to its success are individually tailored PRT programmes and supervised training sessions. The supervised sessions serve two purposes. First, the programme aims to emulate the level of attention received by participants in the previous trials on which the exercise guidelines and *Lift for Life®* programme are based. Second, previous research demonstrates that unsupervised training is less effective in translating to health benefits [12, 36]. Exercise programmes prescribed as part of the *Lift for Life®* programme are individually tailored, so comorbidities or complications (for example, knee osteoarthritis) can be taken into consideration with exercises appropriately modified on a case-by-case basis. Further, to enhance compliance and retention, all participants will receive monthly follow-up phone calls, and will be eligible to receive a reimbursement (as indicated previously) to cover the costs associated with their participation in the programme.

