**Additional measures**				
Anthropometry	Height, weight, body mass index and waist circumference	×	×	×
Physical activity	Community Healthy Activities Model Program for Seniors questionnaire	×	×	×
Diet	Anti-Cancer Council Food Frequency questionnaire	×		×
	24-hour food recollection	×	×	×
Adverse events	Monthly phone calls	Collected from monthly calls		
Programme adherence	Calculated from monthly calendars collected every 8 weeks	Collected every 8 weeks		
Supplement compliance	Calculated from supplement and sachets returned at 3 and 6 months		×	×

HOMA, homeostasis model assessment.

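### The adverse events section contradicts itself on whether all events, or those linked to the training or supplements, are recorded

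*Protocol article*

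**What the plan says.** The Adverse events section of the protocol article has three sentences that bear on recording.

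- The first gives the capture rule: "Any adverse events associated with the exercise programme or supplements will be recorded by the research staff", at the monthly calls.
- The second gives the definition: "an adverse event is defined as any health-related unfavourable or unintended medical occurrence", provided it develops or worsens during observation. It sets no causal condition.
- The third gives the handling rule: "All adverse events will be assessed for seriousness, causality and expectedness by the research staff and recorded and monitored during the trial".

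Table 1, under Additional measures, gives the source of adverse events as "Collected from monthly calls" and sets no limit by cause. The section on the progressive resistance training programme says that "all participants will receive monthly follow-up phone calls", so the calls reach both arms. Both arms do the training. Under Study design, the comparison group receives "no additional powder or supplements", and a placebo powder was considered and rejected.

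**The concern.** The first sentence describes the events to be recorded by their link to the training or the supplements. The third covers every event and orders a causality assessment. Relatedness cannot be both a condition for entry and a judgement made after entry. An event left out because it seemed unconnected is never there to be assessed.

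The design gives this more weight than ordinary loose drafting. The comparison is supplement against nothing, so a symptom that is blamed on the drink has a way into the record in one arm and no equivalent way in the other. This is also a matter of data capture: an analysis plan written later cannot recover an event that was never written down.

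**Working it through.** No arithmetic applies, because the section contains no figure. The check sets the texts side by side.

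**Step 1: the three sentences against each other.**

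| Sentence | Events covered | Action |
|---|---|---|
| First | Those linked to the training or supplements | Recorded at the monthly call |
| Second | Any unfavourable or unintended occurrence | Defined as an adverse event |
| Third | All adverse events | Assessed for causality, recorded, monitored |

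The first and third rows both use the verb for recording and attach it to different sets of events. The first is the only sentence of the section that says what is captured on the calls, and the calls are the only route that Table 1 names. A caller could reasonably work from it alone.

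**Step 2: the consequence under each reading, by arm.**

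| Type of event | First sentence governs: supplement arm | First sentence governs: control arm | Third sentence governs: both arms |
|---|---|---|---|
| Linked to training | Recorded | Recorded | Recorded |
| Symptom attributed to powder or capsules | Recorded | Cannot arise, as nothing is taken | Recorded |
| Same symptom, attributed to neither | Not covered | Not covered | Recorded |

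Under the first reading, take one gastrointestinal symptom that occurs equally often in both arms and has nothing to do with training. In the supplement arm it may be put down to the drink and recorded. In the control arm it has no qualifying cause. An unsuspected harm of the supplements would go unrecorded even in the supplement arm. Under the second reading, both arms are counted alike.

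**Step 3: size.** Suppose the true risk p is the same in both arms, and fractions r1 (supplement) and r0 (control) of events are recorded. The recorded risk ratio is (p × r1) / (p × r0) = r1 / r0. The documents give neither fraction and no event rate, so any figure would only restate an assumed r1 / r0. None is offered.

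**Step 4: reach.** Training-linked events are captured in both arms on either reading. Renal function and routine biochemistry are measured on the same schedule in both arms. The exposure is therefore confined mainly to symptoms and clinical events reported on the calls.

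**The case against.** The strongest reply is that the section already orders full recording. The word *only* does not appear in the first sentence, which can be read as naming the events of most interest and the route of collection, with the definition and general rule following. Table 1 and the calls to every participant fit that reading. This stands as far as it goes: a reader might infer that the plan restricts recording to related events, and the text does not support that. The reply does not remove the conflict, however. It needs the reader to let the third sentence override the first, and nothing in the article says so. Table 1 names the route and not the question asked.

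A reader might also infer that unblinded staff decide what is recorded. That is not established. Under Randomization and blinding, staff who carry out assessments are blinded and supplement distribution rests with the programme coordinator. The article does not say whether the callers are among the blinded staff. Participants do know what they take, and a judgement about supplements may bring that out on the call, but no more can be claimed.

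Finally, a reader might infer that a biased harms comparison is planned. The Statistical analysis section describes no comparison of adverse events between arms, and they are listed among additional measures. A call script and a harms analysis may properly sit in the full protocol or analysis plan, so their absence here is not the point. The point is that two stated recording rules disagree.

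**Conclusion.** The contradiction is real and can be checked within one section. Its effect is conditional. If the first sentence governs practice, attribution filters entry and recorded symptoms are not comparable between a supplement arm and an arm that takes nothing. If the third governs, the wording is untidy and nothing is lost. The documents do not settle which applies, and they give no basis for a size of bias.

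This is a modest point about wording, not a demonstrated flaw in the design. It is worth correcting because events screened out on the calls cannot be recovered and the correction costs almost nothing. According to Trial status, recruitment had already begun, so the rule in use was already shaping the data.

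**What to change.** Reword the first sentence of the Adverse events section to say that all adverse events meeting the definition are recorded in both arms at the monthly calls, using the same question and whatever the suspected cause. State that relatedness to training or supplements is judged afterwards and held in a separate field. If harms are reported by arm, use all-cause events for that comparison. For calls already made, note which rule the callers followed.

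The cost is a change of wording, one common question on calls that already take place, and slightly more events to log. No visit, treatment or sample size changes.

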### Sample size calculations

The sample size is based on the following power calculations from previously published studies of PRT in older adults (including those with type 2 diabetes) [10–12, 36, 38], and work of others that have assessed the independent or combined effects of protein, vitamin D and PRT on the outcome measures [16, 29, 53, 54]. It was estimated that 168 participants would provide 90% power (*P* <0.05 two-tailed test) to detect a 0.5% difference for the change in HbA_1c_ levels between the groups, assuming a conservative standard deviation of 1.1%. For insulin sensitivity, a sample size of 140 would be required to detect a 0.7 difference for the change in HOMA-2 insulin resistance between the groups at a power of 90%, assuming a conservative standard deviation of 1.2. To compensate for a projected 20% drop-out, a total of 202 participants will be recruited to the study and randomized 1:1 to the two groups (101 participants per group).

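### The 20% drop-out allowance multiplies 168 by 1.2 instead of dividing by 0.8, so 202 recruits leave about 162 completers, 6 to 7 short of the plan's own 168; alone, a minor slip

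*Protocol article*

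**What the plan says.** The relevant text is in the protocol article, Methods/Design, Sample size calculations.

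- HbA1c: "It was estimated that 168 participants would provide 90% power" at "<0.05 two-tailed test", "to detect a 0.5% difference for the change in HbA_1c_ levels between the groups", "assuming a conservative standard deviation of 1.1"%.
- HOMA-2 insulin resistance: "a sample size of 140 would be required to detect a 0.7 difference for the change in HOMA-2 insulin resistance between the groups", also at 90% power, "assuming a conservative standard deviation of 1.2".
- Drop-out: "To compensate for a projected 20% drop-out, a total of 202 participants will be recruited to the study", "randomized 1:1 to the two groups (101 participants per group").

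The section gives no other drop-out rate and no other inflation rule. The abstract describes the target only as approximately 200. The Statistical analysis section plans an intention-to-treat analysis with mixed models and says that endpoint measures will be sought from withdrawals where possible. It does not say how many are expected to supply them.

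**The concern.** A drop-out rate is ordinarily a share of those randomised. To keep a required number after such a loss, that number is divided by the share retained. Adding 20% of the required number gives a smaller total, and 202 is exactly what that shortcut produces. The sentence says that 202 compensates for the projected loss; on the article's own figures it does not.

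At stake is the evaluable number for HbA1c, a primary outcome, and how the trial describes its protection against drop-out. The Trial status section says that recruitment is under way, so the statement can still be put right before results are read against it.

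**Working it through.** **Inputs** (all from Sample size calculations): required total 168 for HbA1c and 140 for HOMA-2 insulin resistance; drop-out 20%; recruited total 202, allocated 1:1; HbA1c difference 0.5% with SD 1.1%; HOMA-2 difference 0.7 with SD 1.2; two-sided 5%; power 90%.

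**1. Reproduce the plan's total.**
- Required × (1 + drop-out): 168 × 1.2 = 201.6, rounded up to 202. This matches.
- Required ÷ (1 − drop-out): 168/0.8 = 210. This does not match.
- Starting from 140 gives 140 × 1.2 = 168 or 140/0.8 = 175, so 202 was built on 168.

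**2. What 202 delivers.**
- Completers: 202 × 0.8 = 161.6, about 162 or 81 per group.
- Shortfall: 168 − 161.6 = 6.4 completers, that is 6 to 7; at randomisation, 210 − 202 = 8.
- Drop-out that 202 can absorb while keeping 168: 1 − 168/202 = 0.168, or 16.8%.

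**3. Effect on power** (two-sample t-test, noncentral t, two-sided 5%).

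| Outcome | Per group | Power |
|---|---|---|
| HbA1c, 0.5/1.1 | 84 (168 in total) | 83.4% |
| HbA1c, 0.5/1.1 | 81 (about 162 in total) | 82.0% |
| HbA1c, 0.5/1.1 | 101 (202, no loss) | 89.5% |
| HOMA-2 insulin resistance, 0.7/1.2 | 81 | 95.8% |

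The drop-out step costs 83.4 − 82.0 = 1.4 points for HbA1c. By the normal approximation, the difference detectable with 90% power is (1.960 + 1.282) × 1.1 × √(2/n per group): 0.550% at 84 and 0.560% at 81. The t-test gives 0.553% and 0.564%. For HOMA-2, 162 exceeds the stated 140.

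**4. Where the rest of the gap to 90% comes from.** The normal approximation for HbA1c gives n per group = 2 × (1.960 + 1.282)² × 1.1²/0.5² = 101.7, so 102 per group or 204 in total. The t-test gives 205.4, so 206 in total. The stated 168 is therefore already short of 90% before any drop-out. Two readings come close to it:
- a one-sided 5% t-test at SD 1.1% needs 167.2, so 168;
- a two-sided test at SD 1.0% needs 2 × 84.06 = 168.1 by the normal approximation.

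The article does not show which of these, if either, was used.

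**The case against.** The strongest reply is that drop-outs are not necessarily lost to the analysis. The Statistical analysis section intends to obtain endpoints from withdrawals and to include everyone randomised. HbA1c is measured at baseline, 3 and 6 months, so a late withdrawal can still contribute 3-month data to a mixed model. Of the projected 202 − 161.6 = 40.4 withdrawals, 7 supplying an endpoint would bring the total back to 168. This stands as mitigation: 162 completers is not the same as 162 analysed. It does not rescue the sentence. The sample size section itself treats drop-out as lost numbers and claims that 202 offsets it, and no expected recovery is stated.

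A second reply is that the effect is very small. That is right: 8 recruits and 1.4 power points, with no change to the analysis, the allocation or the HOMA-2 requirement.

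A reader might infer two stronger things. One is that the drop-out slip explains the whole fall from 90% to 82%. It does not, because power at the plan's own 168 is already 83.4%. The other is that the base of 168 came from a wrong SD. The documents do not support that either, since a one-sided test at the stated SD gives 168 as well.

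**Conclusion.** The allowance is miscalculated. On the plan's own 168 and 20%, the total should be 210, and 202 leaves about 162 completers. This holds whatever the origin of the 168. It rests on reading drop-out as a share of those randomised and on counting completers without any recovered endpoints.

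In isolation this is a minor point that should be fixed. The larger discrepancy is the base number, and the two are best corrected together. Raising the total to 210 would repair only the drop-out step: it would leave 168 evaluable and 83.4% power at the stated two-sided inputs. The 95.8% for HOMA-2 is an upper figure, because the Primary outcome measures section excludes glucose and insulin values outside the calculator's validity range, so fewer than 81 per group may be evaluable for that outcome.

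**What to change.** Keep 202 and replace the drop-out sentence with wording such as:

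> 202 randomised with 20% drop-out leaves about 162 with endpoint data (81 per group). This gives about 82% power for a 0.5% HbA1c difference at SD 1.1% (90% power for about 0.56%), and at most about 96% for a 0.7 HOMA-2 insulin resistance difference at SD 1.2, before the HOMA-2 validity-range exclusions.

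In the same edit, correct the claim that 168 gives 90% power, or state the inputs that produce it. If the authors rely on endpoints from withdrawals, they should state the number they expect.

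Stating only that 202 tolerates 16.8% drop-out for 168 evaluable is not enough, because it leaves the 90% claim uncorrected.

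The cost is a short text change and a less favourable power figure. No extra recruitment and no change to the analysis are needed.
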